The effect size assumptions used in the sample size calculation, namely a 50 % reduction in malaria prevalence and a 63 % reduction in vector density, were informed by semi-field experimental hut trials conducted in Muheza, Tanzania [6]. In these trials, 3D-WDS installations captured up to 70.1 % of mosquitoes entering huts, with specific configurations (3D-WDS combined with open eaves) capturing as much as 51.2 % of female *Anopheles* mosquitoes. Although malaria prevalence was not measured directly, reductions in indoor mosquito densities are generally associated with lower malaria transmission risk. Therefore, the assumed 50 % reduction in prevalence represents a plausible extrapolation from the entomological data, based on the expected relationship between vector exposure and infection. This estimate was used as an upper-bound effect size, acknowledging that the actual impact may be more modest under field conditions.

### Social sciences

2.10

A purposive sampling approach was applied for qualitative interviews and FGDs conducted with communities from intervention clusters. Additionally, 50 % of houses were randomly selected from those with 3D-WDS installations across the intervention clusters for structured interviews with the household heads/owners.

### Recruitment

2.11

Community consent for participation in the study was secured through a series of sensitization meetings with village leaders, elders, community health workers, and residents. Introductory letters were sent to the District medical officer of Muheza, and to village leaders, sub-leaders, and hamlet leaders. These meetings introduced the 3D-WDS intervention, explained the concept of mosquito trapping to reduce malaria transmission, outlined the study's objectives, and highlighted the benefits of participation. The meetings also covered epidemiological and entomological procedures, the study timeline, and other practical aspects. Each meeting concluded with a question-and-answer session to address participants' queries, and all were conducted in Kiswahili.

Local carpenters and technicians from the trial villages were recruited for the 3D-WDS installation to enhance community engagement and participation. Following the sensitization meetings, household registration and enumeration were conducted, and a baseline survey and cluster formation followed. Written and verbal consent was obtained from participants prior to epidemiological data collection. During the demographic study, information on housing conditions, house type, GPS location, number of sleeping spaces, and presence of children was collected to determine the number of LLINs and 3D-WDS units required.

Houses in the intervention group that were ineligible for the study received LLINs, and the reason for exclusion from 3D-WDS installation was explained to the household head. From each participating household, a child aged 6 months to 14 years was enrolled in the follow-up cross-sectional survey. If the child was absent, another child from the same household was recruited. Each participating household was assigned a unique identification number, painted in white on the main door, and participating children were also given unique identification numbers for use during the cross-sectional follow-up surveys.

### Cluster selection and randomization

2.12

Clusters were defined as hamlets belonging to villages that comprised more than one, often distantly located, hamlet. During the mapping of the study area, 20 hamlets (clusters) from 17 villages across Muheza District in northeastern Tanzania were identified. These clusters were situated within a 10-km radius of the town of Muheza and were primarily chosen based on their accessibility from the project office, logistical and transportation feasibility, and the presence of houses constructed predominantly using traditional methods and local materials.

The number of houses per cluster ranged from 25 to 107, with a median of 53.5 houses. The mean number of houses was approximately 59.1, with a standard deviation of 20.1. Most clusters had between 40 and 70 houses, with a few outliers at either end of the distribution.

Selection of clusters for the trial was based on the baseline cross-sectional survey conducted to assess malaria prevalence, indoor malaria vector densities, and levels of insecticide resistance across the 20 candidate clusters (Fig. 2). After baseline data analysis, 14 clusters were selected for participation based primarily on malaria prevalence, while also considering vector density and insecticide resistance profiles. A strong positive correlation was observed between the density of female *Anopheles gambiae* and malaria prevalence; therefore, malaria prevalence was prioritized in cluster selection. Clusters falling within one standard deviation of the overall malaria prevalence distribution were included.

These 14 clusters were subsequently randomised into two study arms: seven clusters were allocated to the control arm and seven clusters to the intervention arm for a two-arm cluster randomised controlled trial (cRCT). Randomization was performed in R (version 3.5.2) using the randomizer package (version 1.4.2) [25].

Following randomization, the control clusters had an average of 60.3 households per cluster (range: 40–78), totaling 422 households across the group. The intervention clusters had a slightly lower average of 49.7 households per cluster (range: 34–79), totaling 348 households. This slight discrepancy in household numbers between the two arms was due to eligibility criteria applied specifically to intervention clusters, which did not apply to control clusters. Despite this difference, the number of households remained sufficient and well-distributed for robust comparisons of outcomes between arms.

As randomization was conducted without geographic stratification, the spatial distribution of clusters was not explicitly balanced regarding environmental characteristics such as elevation, land use, or proximity to water bodies. To assess potential geographic imbalances that could influence malaria transmission, we compared key physical and environmental variables across study arms.

The average elevation of clusters was similar between groups: 210.7 m in control clusters and 208.6 m in intervention clusters. Baseline larval habitat mapping also revealed broadly comparable environmental conditions. The most commonly identified larval habitats across both arms were rice plots and swamps, while dominant land use types included pasture and farmland. Vegetation coverage was generally low across all clusters. Accessibility to health services was also comparable, with mean distances and walking times to the nearest health centre being nearly identical between arms.

Although these geographic variables are not central to the intervention itself, they may influence malaria transmission risk and will therefore be included as covariates in the statistical analysis. In the planned mixed-effects models using the lme4 package in R, geographic variables that remain constant within clusters (e.g., elevation, land use type) will be treated as fixed effects, while clusters will be modelled as random intercepts to account for intra-cluster correlation.

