#### Housing condition and participant eligibility

2.2.1

The candidate clusters selected for this study were located within a 10 km radius around the town of Muheza (Fig. 2). Clusters were primarily selected based on accessibility from the project office, logistics and transportation feasibility, population size, and an average of 60–70 houses, built mostly traditionally using local resources. The selected study clusters were at least 2 km apart from any other candidate cluster to avoid potential contamination. All households with at least one child aged 6 months to 14 years old within the cluster were eligible to participate in the study. The main exclusion criteria were households without children between 6 months and 14 years and concrete houses with well-constructed windows. The detailed exclusion and inclusion criteria are outlined in Table 1.

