All households in the intervention clusters were first assessed for eligibility based on predefined inclusion criteria, the main one being the presence of at least one child aged 6 months to 14 years. Additional considerations, such as the structural suitability of the house for 3D-WDS installation, were also applied. Households meeting these criteria were approached for consent to participate in the study, which included both the installation of the 3D-WDS and the screening of eligible children for malaria. Only households that provided informed consent were registered and assigned a unique household identification number. Refusals were rare—only two households declined participation across the seven intervention clusters.

Household registrations were conducted during the sensitization meetings, and each participating house was marked with its unique ID number. The same registered households were approached during each survey round for epidemiological follow-up. From each household, a child aged 6 months to 14 years was enrolled. If the previously screened child was unavailable, another eligible child from the same household was examined. This approach ensured consistency in sampling at the household level while allowing flexibility at the individual level.

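### Eligibility criteria are said to have been applied in intervention clusters only, which conflicts with the study-wide housing exclusions and risks arms that differ in house type with no planned adjustment

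*Protocol article*

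**What the plan says.** All references are to the protocol article.

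- **Section 2.12 (Cluster selection and randomization)** reports that "the control clusters had an average of 60.3 households per cluster (range: 40–78), totaling 422 households across the group". It continues: "The intervention clusters had a slightly lower average of 49.7 households per cluster (range: 34–79), totaling 348 households". It puts the difference down to "eligibility criteria applied specifically to intervention clusters, which did not apply to control clusters", calls it slight, and concludes from the household numbers that comparisons between arms are robust.
- **Section 2.2.1 (Housing condition and participant eligibility)** names no arm: "The main exclusion criteria were households without children between 6 months and 14 years and concrete houses with well-constructed windows". Table 1 likewise lists the housing criteria without distinguishing arms.
- **Section 2.2.2 (Implementation and ethical framework)** describes screening in one arm: "All households in the intervention clusters were first assessed for eligibility based on predefined inclusion criteria". The main criterion there is an eligible child in the household. It then says: "Additional considerations, such as the structural suitability of the house for 3D-WDS installation, were also applied". Two households refused across the seven intervention clusters.
- **Section 2.3.2** says installation left out some brick houses without eaves and concrete houses with iron roofs and well-built windows.
- **Section 2.11 (Recruitment)** says ineligible houses in the intervention group received nets only. It also says that in the demographic study "information on housing conditions, house type, GPS location, number of sleeping spaces, and presence of children was collected".
- **Sections 2.12, 2.14.2 and 2.14.3** name the covariates: age, gender, distance to health centre, monthly precipitation squared, time, and geographic variables such as elevation and land use.

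**The concern.** In a cluster-randomised trial the clusters are comparable by design, but the households analysed within them are comparable only if they are chosen in the same way in both arms. A criterion that operates in one arm breaks that.

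The criterion suggested by the text is not neutral for the outcome. The protocol's own rationale (sections 1.1 and 1.2) is that mosquitoes enter through windows, eaves and other wall openings. The houses left out at installation are those likely to have fewer such openings. If comparable houses stayed in the control arm, the arms differ in a determinant of exposure. That would affect mRDT prevalence, haemoglobin and the light-trap outcomes.

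The balance check in section 2.12 covers elevation, larval habitat, land use, vegetation and access to health care. It does not cover housing. The number of households bears on precision and says nothing about whether the arms contain the same kinds of house.

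**Working it through.** **1. The plan's figures reproduce.** 422/7 = 60.3 and 348/7 = 49.7 households per cluster. The difference is 74 households, and 1 − 348/422 = 17.5%.

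**2. The accounts side by side.** Sections 2.2.1 and Table 1 give housing exclusions for all clusters. Section 2.12 says some criteria applied in one arm only. Section 2.12 does not name them. Section 2.2.2 (screening for structural suitability in intervention clusters), section 2.3.2 (house types left out at installation) and section 2.11 (ineligible intervention houses outside the study) make suitability the likely candidate. Table 1 also requires consent to installation, which can bite only in the intervention arm, but two refusals cannot account for 74 households.

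**3. Could the gap be chance?** For the 20 candidate clusters, "The mean number of houses was approximately 59.1, with a standard deviation of 20.1". Taking this SD as a rough guide, the standard error of a difference between two means of seven clusters is 20.1 × √(2/7) = 10.7. The observed gap is 60.3 − 49.7 = 10.6, about one standard error. The counts alone do not show exclusion; the attribution is the protocol's own statement.

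**4. Does the analysis remove it?** House type is not among the named covariates. A random intercept for cluster absorbs variation between clusters around the arm mean, not a systematic difference between arms. The pooled baseline-to-follow-up test in section 2.14.3 could offset a stable difference if the same households supply both periods. The baseline survey was in June–July 2019 and randomisation in late August 2019 (section 2.8), so baseline data from intervention clusters may include houses later left out.

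**5. Illustration of size.** Let *x* be the share of control houses of the excluded type, and *r* their malaria prevalence relative to eligible houses. Both are assumptions; the document gives neither. With no true effect, the observed prevalence ratio (intervention/control) is 1/[(1 − *x*) + *x r*].

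For *x* = 0.175 and 44% prevalence in eligible houses:
- *r* = 0.3: control prevalence = 0.825 × 0.44 + 0.175 × 0.44 × 0.3 = 0.386. The null ratio is 0.44/0.386 = 1.14. A true 22% gives 0.22/0.386 = 0.57, a 43% reduction.
- *r* = 0.8: control prevalence = 0.425. The null ratio is 1.04. A true 22% gives 0.52, a 48% reduction.

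Null prevalence ratio over a wider grid:

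| *x* | *r* = 0.25 | 0.5 | 0.75 | 1.25 |
|---|---|---|---|---|
| 10% | 1.08 | 1.05 | 1.03 | 0.98 |
| 17.5% | 1.15 | 1.10 | 1.05 | 0.96 |
| 25% | 1.23 | 1.14 | 1.07 | 0.94 |

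With control prevalence held at 44%, this grid corresponds to spurious differences from −2.6 to +10.2 percentage points. A true ratio of 0.50 would be seen as 0.47 to 0.62.

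**6. Power under equal criteria.** Hayes–Bennett formula for proportions (section 2.9 inputs: 44% v 22%, *m* = 50, *k* = 0.3, alpha 0.05 taken as two-sided, 80% power):

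*c* = 1 + (1.96 + 0.84)² × [0.2464/50 + 0.1716/50 + 0.09 × (0.44² + 0.22²)] / 0.22² = 5.89

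This reproduces the planned six clusters per arm. With seven per arm, power is 88.2% at 60.3 v 49.7 per cluster and 87.3% at 49.7 in both arms.

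**The case against.** A reader might infer that concrete houses were removed from one arm and kept in the other, that 17.5% is the share removed, and that the primary comparison is therefore biased by a known amount. The document does not support that.

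- Section 2.12 does not name the criteria, and nowhere is it said that a concrete house was enrolled in a control cluster. If section 2.2.1 and Table 1 were followed in control clusters too, section 2.12 is misworded and the bias is smaller or absent.
- Section 2.2.2 calls an eligible child the main criterion. Any part of the gap made up of childless households does not bias malaria or haemoglobin, since such households contribute no child.
- No household count before exclusion is given by arm, and the gap is about one standard error of chance variation. The largest intervention cluster (79) is slightly larger than the largest control cluster (78).
- Clusters were chosen for mostly traditional housing, which may limit the number of better-built houses.
- The plan is not blind to imbalance: section 2.14.2 compares the outcomes between arms at baseline and section 2.14.3 plans a change-from-baseline test.

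All of this stands as a limit on how strongly the point can be put. It does not dispose of it. The protocol itself says criteria differed by arm, describes structural screening for one arm only, and names no adjustment for housing. The baseline analyses would help only in part, and the document does not say which baseline households enter the change test.

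**Conclusion.** The conflict between section 2.12 and section 2.2.1 with Table 1 is certain. That the arm-specific criterion concerned house structure is a well-supported inference, not a stated fact. On that reading, the plan as written risks selection of households by arm on a determinant of exposure, and nothing it names reliably corrects for this.

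Size and direction are not known. If excluded houses carry less malaria, the bias runs against the intervention; on the illustrative 17.5% and relative prevalence 0.3 to 0.8, it is a modest attenuation. If they carry more, it favours the intervention. The 17.5% is the difference in household counts used as a placeholder, not a documented exclusion share. The sample size is not at fault. The matter should be settled before the primary analysis is final, which is still possible because statistical evaluation is reported as ongoing.

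**What to change.** 1. State which eligibility criteria were applied in each arm and when, with household counts by reason for exclusion, and reconcile section 2.12 with section 2.2.1 and Table 1.
2. Using the housing data already collected (section 2.11), classify control households against the same housing criteria, blind to outcome. Restrict the primary malaria analysis, and the haemoglobin and light-trap analyses, to households that meet them in both arms.
3. Report house type by arm.
4. Add an all-household analysis adjusted for house type as a sensitivity analysis. Note that the survey data may only approximate the on-site judgement of suitability, so some selection may remain.
5. Say which households supply the baseline data in the change-from-baseline test.
6. Remove the statement in section 2.12 that comparisons are robust, since it rests on household numbers alone.

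The cost is a reclassification of existing data and revised analysis-set wording. Some control households leave the primary set: about 74 if control clusters fall to the intervention average. Power at seven clusters per arm would then move from 88.2% to 87.3%.

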### Data collection and management

2.13

#### Epidemiological assessments

2.13.1

The baseline clinical survey was conducted in all 20 candidate clusters during June/July 2019. The main objective of this cross-sectional survey was to determine malaria prevalence and anaemia amongst children aged 6 months to 14 years living in the candidate clusters. The baseline cross-sectional survey was initiated by forming a clinical screening team which comprised a study supervisor, sociologist, clinical officer, nurses, laboratory technicians and a data entry officer. Each screening started with documentation of consent and assent forms by care takers and children above 8 years of age, respectively, by the sociologist. Anthropometric measurements were taken. They included height, weight and mid upper arm circumference (MUAC) (for children under 5 years) followed by measurement of axillary temperature. Malaria infection was diagnosed subsequently using mRDT on blood obtained through finger prick sampling. Anaemia was diagnosed by measuring haemoglobin concentration using a portable β-hemoglobin HemoCue® Hb 201+ photometer (Hemocue®, Ängelholm, Sweden). Finally, blood samples were collected through the same finger prick from all consenting and participating children using Dried blood spot (DBS) technique on a filter paper following WHO guidelines [26] for parasite detection by molecular analysis. For this, a grade 3 Whatman filter paper was cut into a strip of 15 cm × 2.54 cm. Blood samples were collected on one half of the strip, dried and folded. A sticker with information of participant was placed on each DBS card. After each card was fully dried, it was numbered and packaged in a Zip bag with a silica bag enclosed to avoid moisture contamination and stored in −20 °C for subsequent analysis.

Malaria prevalence as a primary outcome of the trial was determined through repeated cross-sectional surveys in 14 study clusters every 10 weeks during the 50-week follow-up period following the procedure described above for the baseline survey. In addition to mRDT, children were also tested for malaria parasitaemia using microscopy. Thick and thin blood smears were obtained to verify the presence of *P. falciparum* and to calculate the parasite density. Thick and thin blood films were prepared, dried, and stained with Giemsa stain, and examined according to WHO guidelines [26,27]. DBS were also collected during the follow-up surveys. Children with malaria positive tests were treated with a standard 3-day course of artemether-lumefantrine (ALu) (Coartem®), an artemisinin combination therapy according to national malaria treatment guidelines set by the National Malaria Control Program (NMCP), Ministry of Health, Tanzania [11,27]. The entire procedure was administered by study nurses and clinical officer, who also gave instructions to the children's caretakers on how to take ALu emphasizing the correct timing for taking ALu tablets and the need to take the drug with a meal**.** During the trial period, the clinical team also provided treatment for non-malaria illnesses, including paracetamol if axillary temperature was ≥37.5 °C, amoxicillin for non-severe pneumonia, oral rehydration salts (ORS) plus zinc for gastroenteritis and ferrous sulphate plus albendazole for anaemia (haemoglobin <9 g/dl). Children below 2 years and those presenting with severe illness at any time were referred to Teule District hospital in Muheza town for further management. Data collection was carried out by data entry officer through pre-devised digital forms using Open Data Kit application (ODK, https://opendatakit.org) in Android tablets.

#### Entomological assessments

2.13.2

Mosquito sampling was carried from all 20 candidate clusters during the baseline and from the 14 study clusters during the follow-up period. A total of 5 cross-sectional surveys were conducted, one every 10 weeks during the 50-week follow-up period. Indoor mosquitoes were collected using CDC-LTs installed in the sleeping spaces of houses by positioning them 50 cm away from the sleepers, who were protected with LLIN. Indoor collections were conducted from 24 randomly selected houses per cluster over six nights, with samples collected from 4 houses each night. CDC-LTs were set in the sleeping area at 18:00 p.m. and removed the following morning at 08:00 a.m.

Trapped mosquitoes were retrieved in the morning and transferred to the sorting facility, where they were identified to species level using standard morphological keys under a microscope [28]. The numbers of *An. gambiae*, *An. funestus* and other anophelines and culicines in the collection were recorded. Gonotrophic status was recorded for all female anophelines, while all males and culicines were discarded. All identified female *An. gambiae* and *An. funestus* mosquito head and thorax carcasses were further subjected to PCR analysis to detect the presence of *Plasmodium falciparum* sporozoites using a melt curve PCR assay to estimate the EIR [29]. A subset (50 %) of morphologically identified female specimens from each CDC-LTs collection were randomly selected for sibling species identification using multiplex PCR [30,31]. In addition, visibly engorged specimens were further subjected to multiplex PCR to determine the sources of blood meal using multiplex PCR method described previously [32].

